## 5.4 MEASURES TO AVOID BIAS

All patients will receive the same treatment in this study.

### 5.4.1 Randomization

Not applicable, since it is a single arm clinical trial.

### 5.4.2 Stratification

Not applicable, since it is a single arm clinical trial.

### 5.4.3 Blinding

Not applicable since it is an open clinical trial.

## 5.5 FORESEEN CALENDAR

- First patient first visit: February 2016
- Inclusion period: 6 months
- Follow-up period: At last 54 weeks (14 months)
- Last patient last visit: October 2017 (End of study)
- Final report submission: April 2018

## 5.6 END OF TRIAL

Stopping rules will be based on the observation of an unexpected high proportion of individuals experiencing SAE or any grade  $\geq 3$  local or systemic events judged definitely or probably related to any of the vaccinations and/or romidepsin administration.

If two or more study participants develop a clinically similar SAE or grade 3 local or systemic event, judged definitely, or probably related to the investigational medicinal products (IMP)s, a review by the Scientific Committee will be requested. The study will be suspended pending review of all safety data. Following this review, the Scientific Committee will make a recommendation to the Principal Investigator and Sponsor regarding continuation of the study (see section 9.3 for details)

In addition, if more than 50% of participants withdraw from the Scientific Committee will discuss a premature stop of the trial.

The date of the end of the trial will be to the last visit of the last patient.

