## 5.3 ENDPOINTS

### 5.3.1 Primary endpoint(s)

1. Safety and tolerability evaluation as measured by  $\geq 3$  grade adverse events (AE) and serious adverse events (SAE).
2. Reduction of the viral reservoir measured in CD4+ T cells by digital droplet PCR (ddPCR) at baseline and 1 week after 3rd dose of RMD (total HIV-1 DNA copies per  $10^6$  CD4+ T cells)

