#### 9.4.1 Seriousness

A SAE is any AE occurring at any dose that:

- Results in death;
- Is life-threatening (i.e., in the opinion of the Investigator, the subject is at immediate risk of death from the AE);
- Requires inpatient hospitalization or prolongation of existing hospitalization (hospitalization is defined as an inpatient admission, regardless of length of stay);

- Results in persistent or significant disability/incapacity (a substantial disruption of the subject's ability to conduct normal life functions);
- Is a congenital anomaly/birth defect;
- Constitutes an important medical event.

Important medical events are defined as those occurrences that may not be immediately life threatening or result in death, hospitalization, or disability, but may jeopardize the subject or require medical or surgical intervention to prevent one of the other outcomes listed above. Medical and scientific judgment should be exercised in deciding whether such an AE should be considered serious.

Events **not considered** to be SAEs are hospitalizations for:

- A standard procedure for protocol therapy administration. However, hospitalization or prolonged hospitalization for a complication of therapy administration will be reported as an SAE.
- Routine treatment or monitoring of the studied indication not associated with any deterioration in condition.
- A procedure for protocol/disease-related investigations (e.g., surgery, scans, endoscopy, sampling for laboratory tests, bone marrow sampling). However, hospitalization or prolonged hospitalization for a complication of such procedures remains a reportable SAE.
- Hospitalization or prolongation of hospitalization for technical, practical, or social reasons, in absence of an AE.
- A procedure that is planned (i.e., planned prior to starting of treatment on study); must be documented in the source document and the CRF. Hospitalization or prolonged hospitalization for a complication remains a reportable SAE.
- An elective treatment of a pre-existing condition unrelated to the studied indication.
- Emergency outpatient treatment or observation that does not result in admission, unless fulfilling other seriousness criteria above.

If an AE is considered serious, both the AE page/screen of the CRF and the SAE Report Form must be completed.

For each SAE, the Investigator will provide information on severity, start and stop dates, relationship to IP, action taken regarding IP, and outcome.

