#### 9.4.2 Severity / Intensity

For both AEs and SAEs, the Investigator must assess the severity / intensity of the event.

Intensity will be assessed by the investigator using the following terms according to the Division of AIDS table for grading the severity of adult and pediatric adverse events (Attachment O):

- Grade 1 = Mild
- Grade 2 = Moderate
- Grade 3 = Severe
- Grade 4 = Life threatening
- Grade 5 = Death

The term “severe” is often used to describe the intensity of a specific event (as in mild, moderate or severe myocardial infarction); the event itself, however, may be of relatively minor medical significance (such as severe headache). This criterion is *not* the same as “serious” which is based on subject/event *outcome* or *action* criteria associated with events that pose a threat to a subject’s life or functioning.

Seriousness, not severity, serves as a guide for defining regulatory obligations.

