## 9.7 SCIENTIFIC COMMITTEE

A Scientific committee will be formed to review clinical data and stopping rules. The committee will be composed of the coordinating investigator plus two physicians of the investigator team and one external physician. See attachment P for details

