## 10 STATISTICS

The primary safety and tolerability analysis will include a description and summary of the number and percentage of grade  $\geq 3$  AE and SAE; their grading and imputability for both MVA.HIVconsV and RMD administrations.

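### The counted suspension trigger in 5.6 says grade 3 where the sentence it implements says grade ≥3, and 10.2(a) restates the rule with no grade and a Part A limit

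*Protocol*

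**What the plan says.** Section 5.6 of the Protocol sets the trial-wide safety rule in two steps.

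- **Principle.** The stopping rules look for an unexpectedly high share of participants with an SAE or any grade ≥3 "local or systemic events judged definitely or probably related to any of the vaccinations and/or romidepsin administration".
- **Count.** The next sentence makes this operational: "If two or more study participants develop a clinically similar SAE or grade 3 local or systemic event", definitely or probably related to the investigational products, a Scientific Committee review is requested and the study is suspended until the safety data have been reviewed. This is the only counted safety-event trigger in 5.6. The committee then gives a recommendation "regarding continuation of the study (see section 9.3 for details").

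The safety endpoint and its analysis use grade ≥3. Primary endpoint 1 (5.3.1) is defined by ≥3 "grade adverse events (AE) and serious adverse events (SAE"). The opening of section 10 promises a "description and summary of the number and percentage of grade" ≥3 AEs and of SAEs. Section 10.3 takes the incidence of grade ≥3 events or SAEs as the safety measure.

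Section 10.2 announces stopping rules for both parts of the study. Item a) refers to the 5.6 rule, words it as any AE or SAE after any vaccination or romidepsin, gives no grade, and places it in Part A. Item b) holds only individual immunogenicity and viremia criteria for the antiretroviral pause. Section 5.2 and Attachment A put the second vaccination, MVA2, in Part B.

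**The concern.** The counted sentence decides when review and suspension of a phase I trial become mandatory. It should be at least as sensitive as the principle it implements and the endpoint it protects. As worded it stops at grade 3 and relies on the SAE limb to catch anything worse, so a worse event can count for less than a milder one.

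The same rule also appears in three wordings: grade ≥3 (5.6, first sentence), grade 3 (5.6, second sentence) and no grade at all (10.2(a)). The third adds a Part limit that 5.6 does not have. A site or committee member working from section 10.2 could reasonably ask whether a reaction to MVA2 counts.

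**Working it through.** No figure in the protocol bears on this point, so the check is a comparison of text.

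**Step 1: which events the grade wording leaves out.** Take two participants with clinically similar events, each judged definitely or probably related, and count under each wording. Suspension needs a count of 2.

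| Pair of events | Count at SAE or grade 3 | Count at SAE or grade ≥3 |
|---|---|---|
| Grade 3 and grade 3 | 2: suspend | 2: suspend |
| Grade 3 and SAE | 2: suspend | 2: suspend |
| Serious grade 4 and serious grade 4 | 2: suspend | 2: suspend |
| Grade 3 and non-serious grade 4 | 1: no trigger | 2: suspend |
| Non-serious grade 4 and non-serious grade 4 | 0: no trigger | 2: suspend |

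The two wordings differ only where a grade 4 event is not classed as serious. Grade 5 is death, which is always an SAE.

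**Step 2: whether a non-serious grade 4 event can exist under this protocol.**

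- Section 9.4.2 labels grade 4 as life threatening, and 9.1 and 9.4.1 make a life-threatening event an SAE. That covers most cases.
- Section 9.4.2 still keeps the two scales apart: "Seriousness, not severity, serves as a guide for defining regulatory obligations".
- For important medical events, 9.4.1 leaves the classification open: "Medical and scientific judgment should be exercised in deciding whether such an AE should be considered serious".
- Section 9.5 says that a laboratory abnormality of any grade needs documenting as an SAE only if it meets a seriousness criterion.
- The diary scales in 8.4.4 and 8.4.5 include in grade 4 an inability to carry out basic self-care. That is not a listed seriousness criterion in those terms.

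The set is therefore narrow but not empty by definition.

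**Step 3: scope by Part.**

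| Section | Events | Part |
|---|---|---|
| 5.6, first sentence | SAE or grade ≥3, any vaccination or romidepsin | no limit |
| 5.6, counted trigger | SAE or grade 3, any investigational product | no limit |
| 10.2(a) | any AE or SAE, any vaccination or romidepsin, citing 5.6 | Part A |
| 10.2(b) | individual immunogenicity and viremia criteria | before the pause |

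Part A contains one vaccination, yet 10.2(a) speaks of vaccinations in the plural and defers to 5.6. Trial-wide scope is the more natural reading, and the words that limit the rule to Part A contradict it.

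**Step 4: size.** The only event rate in 10.3 is a probability below 0.1 for grade 3 and 4 AEs combined. It does not separate grade 4, still less non-serious grade 4. No probability of a missed trigger can be derived from the documents.

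**The case against.** The strongest reply is that the grade gap has almost no practical effect. Grade 4 means life threatening, which is an SAE. The clinical grade 4 descriptions in the diaries can mostly be mapped to a seriousness criterion, such as substantial disruption of normal life functions or action needed to prevent a serious outcome. The clearest counter-example is a laboratory value, and it is arguable whether that is a local or systemic event at all. A committee told to act on two grade 3 events would hardly ignore a grade 4.

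Much of this stands, and it is why the point is minor. It shows that the gap is small, not that the wording is right. Mapping an event to seriousness is a judgement, whereas the trigger is meant to be mandatory. Section 9.7 does give a wider remit ("A Scientific committee will be formed to review clinical data and stopping rules"), and the individual holds in 7.3.1 and 7.3.2 protect the affected participant. Neither fixes when trial-wide suspension must happen. Section 9.8.4 sends SAEs to the coordinating investigator so that the committee can be called; section 9.8 describes no such route for non-serious events. The doubt about laboratory values is fair, and the grade correction alone does not settle it.

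On scope, a reader might infer that the protocol has no safety stopping rule after MVA2, or that similar reactions to MVA1 and MVA2 would not be added together. The documents do not support that. Section 5.6 has no Part limit, 10.2(a) cites it, and neither 9.7 nor 9.8.4 is limited by Part.

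**Conclusion.** The point holds as a wording error in a decision threshold. The counted trigger in 5.6 is narrower than the sentence it implements, primary endpoint 1, the opening of section 10 and section 10.3. Section 10.2(a) contradicts 5.6 on grade and on Part. Confidence in the mismatch is high.

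The consequence is small: it reaches only related grade 4 events not classed as serious, and the likely intent on scope is clear. A reader might infer that life-threatening events escape the rule. They do not, because they enter as SAEs. The pointer in 5.6 to section 9.3, which deals with AE documentation, is a clerical slip and does not affect the rule.

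The conclusion assumes a literal reading of the trigger. It also assumes that the attachments not shown, in particular the grading table (Attachment O) and the committee details (Attachment P), do not already settle the matter.

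**What to change.** - **Section 5.6:** in the counted sentence write *SAE or grade ≥3 local or systemic event*, and state that clinically similar grade 3 and grade 4 events count together.
- **Section 10.2(a):** use the same grade wording, and either delete the limit to Part A or state that the 5.6 rule applies after every dose of an investigational product, including MVA2.
- **Clerical:** correct the reference to 9.3. Section 9.7, which describes the committee, is the likely target.

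The cost is a few words in two sections. The downside is a slightly higher chance of a committee review and a temporary suspension, which the first sentence of 5.6 already implies.

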##### Definitive:

- A plausible time sequence exists in relation to administration of the drug or its plasma or tissue concentrations.
- The observed manifestation coincides with the known adverse reactions profile of the implicated drug.
- The event cannot be explained by the concurrent disease or by other drugs or chemical substances.
- Response to withdrawal must be clinically plausible, i.e., the condition improves on discontinuing administration of the drug.
- A positive response to repeat exposure is observed.

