##### Probable:

- A reasonable time sequence exists in relation to administration of the drug.
- The observed manifestation coincides with the known adverse reactions profile of the implicated drug.
- The event is unlikely to be explained by the concurrent disease or by other drugs or chemical substances.

- Response to withdrawal is clinically plausible, i.e., the condition improves on discontinuing administration of the drug.
- No repeat exposure is required to complete this definition.

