**Possible:**

- A reasonable time sequence exists in relation to administration of the drug.
- The observed manifestation coincides with the known adverse reactions profile of the implicated drug.
- The event might be attributable to the clinical condition of the patient or to other concomitantly administered drugs or chemical substances.
- Information concerning drug withdrawal may be unavailable or confusing.

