## 9.8 EXPEDITED REPORTING OF ADVERSE EVENTS

### 9.8.1 Reporting to Regulatory Authorities and the Ethics Committee

The sponsor will inform the Spanish Medicines Agency (Ministry of Health), the competent authorities of the autonomous region and the Ethics Committees implicated in the clinical trial about any important information of security of the IMPs.

The sponsor will inform the Spanish Medicines Agency (Ministry of Health) of any SUSAR which may be related to the study treatment.

The sponsor will inform competent authorities of the implicated autonomous region of any SUSAR which may be related to the study treatment, and that have been happened in patients in its autonomous region.

The sponsor will inform the Ethics Committee of any SUSAR which may be related to the study treatment, and that have been happened in patients included in its sphere of action.

The Sponsor will inform relevant Regulatory Authorities and Ethics Committees;

- Of all relevant information about SUSAR that are fatal or life-threatening as soon as possible, and in any case no later than 7 days after knowledge of such a case. Relevant follow-up information for these cases will be subsequently be submitted within an additional eight days
- Of all other SUSAR as soon as possible, but within a maximum of 15 days of first knowledge by the investigator.

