#### 9.8.4 Reporting by Sponsor to Coordinating investigator

The Sponsor will inform the Coordinating investigator of all SAEs within 24 hours in order that the Coordinating investigator can call the scientific committee to assess trial stopping rules.

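### Section 5.6 makes suspension mandatory only for two or more participants with similar related events, so one related death or life-threatening event obliges no dosing pause for the others

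*Protocol*

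**What the plan says.** Section 5.6 of the protocol opens with a general statement that stopping depends on an unexpectedly high proportion of participants with SAEs or related events of grade 3 or more. It gives no number. The operative rule follows: "If two or more study participants develop a clinically similar SAE or grade 3 local or systemic event", judged definitely or probably related to the products, leads to a Scientific Committee review, and the study is suspended until all safety data have been reviewed. The committee then makes a recommendation "regarding continuation of the study (see section 9.3 for details".

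Section 10.2 a) repeats the high-proportion idea for Part A and refers back to 5.6.

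Other provisions that bear on a single grave event:
- Sections 7.3.1 and 7.3.2 list grounds on which a participant might be discontinued or postponed. They include a possibly, probably or definitely related SAE, and a risk to the volunteer in the opinion of the investigator or sponsor.
- Section 9.8.4 has every SAE passed to the coordinating investigator within 24 hours "in order that the Coordinating investigator can call the scientific committee to assess trial stopping rules".
- Section 9.8.1 requires fatal or life-threatening SUSARs to be notified "as soon as possible, and in any case no later than 7 days after knowledge of such a case".
- Section 9.4.1 defines life-threatening as meaning that "in the opinion of the Investigator, the subject is at immediate risk of death from the AE".

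**The concern.** The mandatory rule works by repetition: a second participant must have a clinically similar event. That suits moderately severe reactions, where one case may be chance. It does not suit a related death or an immediately life-threatening event, where the usual reason for a rule is to protect the next participant before a second case appears.

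Section 10.3 says information on adverse event rates with romidepsin at this dose is still scarce. The infusions are one week apart (weeks 3, 4 and 5), so another participant in mid-cycle can be due a dose soon after a grave event. Whether that dose is given would rest on judgement and not on a written rule.

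**Working it through.** The protocol states no operating characteristic for the stopping rule, and the maximum of 24 is the size of the parent cohort, so there is no figure to reproduce. The check is a reading of the text, followed by a count of the doses at issue.

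**1. The trigger.** Suspension under 5.6 needs all of: at least two participants; clinically similar events; an SAE or grade 3 event; a definite or probable causal judgement. With one affected participant the first condition fails, whatever the event. The opening sentence does not help: one participant in 24 is 4%, and no threshold is given.

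**2. The other provisions.**

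| Section | What it provides | Obliges a pause for the others? |
|---|---|---|
| 10.2 a) | Refers back to 5.6 | No |
| 7.3.1, 7.3.2 | Holds that might be applied, at discretion; the volunteer-safety ground is not limited to the affected participant | No, but permits one |
| 9.8.2, 9.8.4 | Investigator to sponsor in 24 hours, sponsor to coordinating investigator in 24 hours; the committee can then be called | No, and the rules it would assess are those of 5.6 |
| 9.8.1 | Notification of authorities and ethics committees | No |
| 9.7 | Committee reviews clinical data and stopping rules | No further trigger |

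The reference in 5.6 to 9.3 leads to adverse event documentation and adds no criterion.

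**3. Causality (supporting point only).** Under 9.4.3, Probable requires "Response to withdrawal is clinically plausible, i.e., the condition improves on discontinuing administration of the drug". Definitive requires improvement on withdrawal too, and also "A positive response to repeat exposure is observed". Applied literally, a death meets neither, can be rated at most Possible, and would not count towards the trigger. Definitive, Probable and Possible also share the condition "The observed manifestation coincides with the known adverse reactions profile of the implicated drug", which an unforeseen reaction fails. Sections 8.4.4 and 8.4.5, however, use a second scale (unrelated, unlikely, possibly, probably, definitely) without these conditions.

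**4. Doses at issue.** Inputs: 24 participants (10.3), 6-month inclusion (5.5, taken as 26 weeks), doses at weeks 0, 3, 4, 5 and 9 (6.3). Assumption: even enrolment, so spacing is 26/24 = 1.083 weeks. Take an event at week 3 of participant k, in mid-trial. The other enrolled participants with doses left are:
- k+2, at week 3 − 2 × 1.083 = 0.83: 4 doses left
- k+1, at week 3 − 1.083 = 1.92: 4 doses left
- k−1, at week 3 + 1.083 = 4.08: 2 doses left
- k−2, k−3, k−4 and k−5, at weeks 5.17, 6.25, 7.33 and 8.42: 1 dose each

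Total: 4 + 4 + 2 + 4 × 1 = 14 doses in 7 people.

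Due within 7 days:
- k+3, first vaccination: (3 × 1.083 − 3) × 7 = day 1.8
- k−5, second vaccination: (9 − 8.42) × 7 = day 4.1
- k−1, third romidepsin infusion: (5 − 4.08) × 7 = day 6.4

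The first of these is a new participant, outside the 14. So one romidepsin infusion falls within the week. Within the 48 hours of the two reporting steps only the new participant's first vaccination falls due. These timings depend on the assumed spacing.

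**The case against.** The strongest reply is that unreflective dosing after a death is unlikely here. All product is given at one unit (6.3). A study physician reviews and prescribes before each dose (8.1.2, 8.1.4, 8.1.6, 8.1.8, 8.1.11). Romidepsin recipients are observed for 24 or 12 hours (6.3.1). Every SAE should reach the coordinating investigator, who sits on the committee (9.7), within two 24-hour steps. The 7 days in 9.8.1 are an outer limit for notification, not the time in which the trial would react. Attachment P, cited in 9.7 for details of the committee, is not shown.

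Much of this stands. A reader might infer that nothing in the protocol can stop dosing after one grave event. That is wrong: 7.3.1 and 7.3.2 permit holds, including for unaffected participants. What remains is that a pause is permitted and nowhere required.

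A reader might also infer that a death can never count towards the trigger. The documents do not support that firmly. The diary-section scale has no withdrawal condition, and its terms are closer to those of 5.6. Section 9.1 defines related reactions that do not match the product information, which conflicts with a literal known-profile test. A life-threatening event that resolves can be rated Probable if it fits the known profile.

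**Conclusion.** The point holds in a narrow form: after one related fatal or life-threatening event, the protocol text obliges no pause in dosing of the other participants. This rests on the wording of 5.6 and on the absence of a mandatory pause in the sections compared above, not on a probability. The causality definitions add support for deaths if 9.4.3 is applied literally, and no more than that.

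The size is modest. Under even enrolment, about 14 doses in 7 enrolled participants are left to discretion at such a moment, with one romidepsin infusion due within a week. A reader might instead count every dose still planned in the trial. For an event in the 6th participant, those not yet enrolled would add (24 − 8) × 5 = 80 doses, but these people have not started and could simply not be started, so that total overstates the exposure. Nor can a chance of the situation arising be given. Section 10.3 offers only a bound below 0.1 for grade 3 or 4 events with the vaccine and no romidepsin rate.

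This should be changed because the remedy is cheap, not because the trial is otherwise unprotected. The mismatch between grade 3 and grade 3 or more within 5.6 is clerical, since deaths and immediately life-threatening events are already SAEs. The reference to 9.3 where 9.7 is meant is clerical too.

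**What to change.** In 5.6, keep the similar-event trigger and add one sentence, which 10.2 a) then takes in by reference:

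> Any single fatal or life-threatening event (as defined in 9.4.1) judged at least possibly related to an IMP, or for which an IMP cause cannot be excluded, suspends further dosing of all participants pending Scientific Committee review.

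The wider causality wording avoids dependence on the 9.4.3 definitions. Tying the rule to 9.4.1, which requires immediate risk of death, keeps an asymptomatic grade 4 laboratory value from suspending dosing by itself. In the same amendment, write grade 3 or more in the trigger and correct the cross-reference to 9.7.

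The change uses the existing committee and the existing 24-hour reporting. Its cost is an occasional pause, sometimes for an event later judged unrelated. A pause may outlast the 7-day romidepsin or 10-day vaccination postponement window for the few participants in mid-schedule. Participants cannot be replaced (7.3.7), so some could lose their planned sequence and, in mid-romidepsin, their reservoir endpoint.
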